# Short or Long Antibiotic Regimes in Orthopaedics (SOLARIO): a randomised controlled open-label non-inferiority trial of duration of systemic antibiotics in adults with orthopaedic infection treated operatively with local antibiotic therapy

**DOI:** 10.1186/s13063-019-3832-3

**Published:** 2019-12-09

**Keywords:** Osteomyelitis, Prosthetic joint infection, Diabetic foot, Antibiotic, Duration, Carrier, Revision, Local antibiotic therapy

## Abstract

**Background:**

Orthopaedic infections, such as osteomyelitis, diabetic foot infection and prosthetic joint infection, are most commonly treated by a combination of surgical debridement and a prolonged course of systemic antibiotics, usually for at least 4–6 weeks. Use of local antibiotics, implanted directly into the site of infection at the time of surgery, may improve antibiotic delivery and allow us to shorten the duration of systemic antibiotic therapy, thereby limiting the frequency of side effects, cost and selection pressure for antimicrobial resistance.

**Methods:**

SOLARIO is a multicentre open-label randomised controlled non-inferiority trial comparing short and long systemic antibiotic therapy alongside local antibiotic therapy. Adult patients with orthopaedic infection, who have given informed consent, will be eligible to participate in the study provided that no micro-organisms identified from deep tissue samples are resistant to locally implanted antibiotics. Participants will be randomised in a 1:1 ratio to receive either a short course (≤ 7 days) or currently recommended long course (≥ 4 weeks) of systemic antibiotics. The primary outcome will be treatment failure by 12 months after surgery, as ascertained by an independent Endpoint Committee blinded to treatment allocation. An absolute non-inferiority margin of 10% will be used for both per-protocol and intention-to-treat populations. Secondary outcomes will include probable and definite treatment failure, serious adverse events, treatment side effects, quality of life scores and cost analysis.

**Discussion:**

This study aims to assess a treatment strategy that may enable the reduction of systemic antibiotic use for patients with orthopaedic infection. If this strategy is non-inferior, this will be to the advantage of patients and contribute to antimicrobial stewardship.

**Trial registration:**

Clinicaltrials.gov, NCT03806166. Registered on 11 November 2019.

## Background

The overuse of antibiotics contributes to healthcare costs, adverse drug reactions and the rising threat of antibiotic resistance. In 2016, antibiotic use in England alone cost > £200 million [1]. Around one in six patients treated with antibiotics for chronic osteomyelitis experience adverse drug reactions [2, 3] and bacterial resistance to broad-spectrum last resort antibiotics, such as carbapenems, has risen substantially in the UK over the past 10 years, driven by evolution under selection pressure from systemic antibiotic use [4, 5]. Furthermore, exposure to systemic antibiotic therapy increases the risk of subsequent antibiotic-resistant infection [6–8]. Consequently, the recommended duration of treatment for many common infectious diseases has been reduced in recent years [4, 5].

Orthopaedic infections include osteomyelitis, prosthetic joint infection, fracture-related infection and diabetic foot infection. Treatment usually involves surgery combined with antibiotics. Systemic antibiotics alone are commonly ineffective, primarily due to the persistence of bacteria in biofilm on bone and implant surfaces. Antibiotics penetrate biofilm poorly, where bacteria additionally express a quiescent metabolic state that confers antibiotic tolerance [9]. Consequently, at least 4–6 weeks of postoperative oral or intravenous antibiotics are currently recommended for orthopaedic infections, which is much longer than for common soft-tissue bacterial infections [10–13].

Increasingly, systemic antibiotics are now being used in combination with local antibiotic therapy delivered directly to the site of orthopaedic infection at the time of surgery [14–21]. Local antibiotic therapy allows high concentrations of antibiotic to be delivered rapidly to the bone and surrounding tissue with limited risk of systemic absorption and consequent side effects [14, 15, 20, 22–25]. Modern bioabsorbable ceramic carriers are able to elute therapeutic concentrations of antibiotic for > 7 days, based on pharmacokinetic studies [26–29]. Hence, local antibiotic therapy may allow much shorter courses of systemic antibiotics to be used for orthopaedic infection [26, 30–34] but, in the absence of prospective comparison with longer courses, this approach has not been widely adopted.

Previous trials [35–37] that have compared local antibiotic therapy against systemic antibiotic treatment for orthopaedic infection have been limited by low numbers and potential bias due to deviation from the allocated treatment strategy. Many people treated for orthopaedic infection now receive local antibiotic therapy as part of routine surgical treatment which allows the comparison of standard long courses of systemic antibiotic treatment for these patients with short course treatment within routine clinical care.

## Methods

### Objectives

#### Primary objective

The primary objective of the present study is to determine whether treatment of orthopaedic infection with local antibiotics combined with ≤ 7 days of systemic therapy (oral or intravenous) is non-inferior to treatment with local antibiotics combined with ≥ 4 weeks of systemic therapy (oral or intravenous), as assessed by treatment failure rate at one year.

#### Secondary objectives

Secondary objectives of the present study are to compare the following secondary endpoints according to treatment allocation:
probable treatment failure and possible treatment failure;serious adverse events (SAEs), including death (i.e. all-cause mortality);antibiotic side effects related to the treatment of orthopaedic infection;resource allocation using (a) length of inpatient hospital stay, (b) frequency of outpatient visits, (c) antibiotic prescribing costs. In-hospital treatment cost analysis;quality of life as evaluated by the patient-reported outcome measures on the EQ-5D-5 L questionnaire at baseline and one-year follow-up;deviation from allocated treatment strategy, including additional antibiotic prescribing, and early termination of systemic antibiotics because of AEs, patient preference or any other reason.

### Study design

SOLARIO is a parallel-group, open-label study randomising individual participants to short or long systemic antibiotic regimes, each in combination with local antibiotic therapy. The primary endpoint is definite treatment failure at 12 months. Any post-randomisation readmission or reoperation with signs or symptoms at the anatomical site of infection will be considered a potential treatment failure. An independent Endpoint Committee, blind to allocation, will review all potential treatment failures to determine whether a primary or secondary infection-related endpoint has been reached.

The choice of antimicrobial agents used will not be dictated by the trial protocol. Choice of specific agents, both local and systemic, will be as determined by the clinician caring for the patient, and will be chosen according to the available clinical and microbiological data, local epidemiology and good clinical practice.

### Participants

This study will recruit adults undergoing surgical treatment for orthopaedic infection where the surgery includes the implantation of a licensed local antibiotic-carrier combination at the site of infection.

### Study centres

This multicentre study will take place across multiple orthopaedic centres with expertise and experience of providing specialist care for orthopaedic infection in the UK and mainland Europe. A full list of active study sites is available at www.clinicaltrials.gov (NCT03806166, registered on 11 January 2019).

### Eligibility criteria

A patient must meet ALL of the following criteria to take part:
Provision of informed consent within seven days after surgery;Aged ≥ 18 years;Presenting with an orthopaedic infection as defined by one or more of the following criteria:
localised pain, ORlocalised erythema, ORtemperature ≥ 38.0 °C, ORa discharging sinus or wound;
4)Undergoing surgical treatment for the infection;5)Locally administered licensed antibiotic-carrier combination(s) at the site of orthopaedic infection;6)Would ordinarily be managed with a prolonged course (≥ 4 weeks) of systemic antibiotic(s);7)Specimens for microbiological analysis taken at index surgery.

All patients included in the study will have a maximum of seven days of systemic antimicrobial therapy, as randomisation has to be within seven days.

A patient may not enter the study if ANY of the exclusion criteria listed below apply.

#### Surgical exclusion criteria

The index operation was not a definitive procedure with the aim of eradicating infection:
Primary closure has not been achieved, orRe-look surgery is planned;The index operation involved implant retention at the site of index infection (e.g. Debridement, Antibiotics and Implant Retention).

#### Microbiological exclusion criteria

3)Any identified micro-organisms from operative specimens from the site of index infection that are fully resistant to the local antibiotic(s) administered at the site of infection.

#### Medical exclusion criteria

4)Any other infection necessitating additional systemic antibiotic treatment > 7 days after surgery, such as *Staphylococcus aureus* bacteraemia or bacterial endocarditis;5)If the patient is in a clinical trial involving an Investigational Medicinal Product (IMP) related to infection.

### Interventions

The intervention assessed in this study is the reduction of the duration of systemic antibiotic therapy from ≥ 4 weeks to ≤ 7 days. All patients will have local antibiotic therapy given at the time of surgery as part of their planned treatment.

### Concomitant care and interventions permitted in parallel

Clinical care for the participant, other than the duration of systemic antibiotic treatment for orthopaedic infection, will not be influenced by participation in this study. All treatment decisions will be made by the participant in partnership with the clinical care team.

### Outcomes

Endpoints will be identified by prospective surveillance throughout the year after randomisation. This study is an open-label trial, but the ascertainment of outcomes will be carried out by an endpoint committee who will be blind to the participant’s treatment allocation (blinded Endpoint Committee).

The definitions of infection recurrence used in this study are based on internationally accepted standards [9, 10, 38] with minor modifications. They have been applied in a previous study in orthopaedic infection [3].

### Primary endpoint

The primary endpoint will be definite treatment failure within 12 months of surgery, as determined by a blinded Endpoint Committee using notes from the patient records redacted for names of patients and clinicians, as well as information that might betray the allocated treatment strategy. The criteria for definite, possible and probable treatment failure are available in the Additional file 1.

### Secondary endpoints

Secondary endpoints include probable and possible treatment failure, as determined by the blinded Endpoint Committee. Definitions and information about validation for these endpoint measures are available in the Additional file 1. Additional secondary endpoints, discussed below, will be determined by the research team at individual sites.

Symptoms potentially attributable to side effects of antibiotic treatment will be recorded on a three-point scale (absent, mild, severe) for all participants, regardless of whether antibiotics are taken at the time [39]. Five potential side effects, identified as having the highest impact by a group of 16 patient representatives, will contribute to a bivariate analysis; all additional reported symptoms that may represent antibiotic-related side effects will be similarly recorded on the three-point scale and reported as proportions of participants affected.

Quality of life will be assessed using the EQ-5D-5 L questionnaire administered at study enrolment and 12 months after surgical treatment of infection. For the enrolment questionnaire, patients will be asked to describe their health state immediately before index surgery. The mean difference between quality of life scores at baseline and 12 months will be compared. Permission to use the EQ-5D-5 L questionnaire was granted by the EuroQol Research Foundation.

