**Fig. 2 Fig2:**
[figure not shown]
SPIRIT Schedule of enrolment, interventions and assessments in the SOLARIO study

Local clinical research staff will seek informed consent to participate in the study from eligible patients. After receipt of the Patient Information Sheet, potential participants will be encouraged to discuss the study with the clinical care team and/or personal contacts and to ask questions. The Patient Information Sheet and Informed Consent Form state clearly that taking part in the study is voluntary and that refusal or withdrawal carry no detriment to usual clinical care. Patients not felt to have capacity to consent to study participation will not be approached and proxy consent will not be allowed. This trial does not involve any study-specific outpatient appointments, investigations or hospital visits. Hence, there will be no expenses or other payments to participants in this study.

Potential participants will be afforded up to seven days after their surgery to decide whether they wish to take part. Those that provide fully informed consent will be randomised through a centralised electronic database with stratification by study site only.

Participants will be followed up during routine care visits at the local centre. The frequency and timings of routine care visits will vary depending on the clinical condition and management pathways of individual patients. Trial-specific data collection points will be at: (1) 6 weeks (± 1 week); (2) once between 3 and 6 months; and (3) 1 year (± 1 month) after randomisation. There will be no trial-specific clinic visits. Either the patient or the patient’s GP will be asked for follow-up data if information relating to outcome measures is not available through routine care visits at these times.

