#### Bivariate analysis

The potential advantage of short systemic antibiotics (fewer side effects) versus the potential disadvantage (higher treatment failure rate) will be summarised at the patient level in an advantage score.

The advantage score is defined as the sum of predefined side effect scores at the first two follow-up timepoints: a 1-point increase is equivalent to, in either follow-up period, one level higher for one of each of the five predefined side effects or the presence of either *Clostridium difficile* diarrhoea or intravenous catheter-associated complication. A formal assessment of the difference between the two arms with respect to the advantage score will be based on the difference in mean values with a 95% confidence interval and a *p* value for the test of the null hypothesis of no difference between the treatment groups.

In addition, the difference in mean advantage score and the difference in treatment failure rate will be plotted in a two-dimensional plane together with a 95% confidence region. Furthermore, the ration between the scores will be reported together with a 95% confidence interval. This will allow assessment of the improvement in mean advantage score required for one more treatment failure in 100 patients in order to regard short systemic antibiotic treatment as beneficial. Further secondary analyses are described in Additional file 1.

Data monitoring, interim analysis and criteria for early discontinuation of the study are described in Additional file 1.

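### The quality-of-life comparison is stated as change from baseline with no baseline adjustment; adjusting the 12-month score for baseline would be more precise at no cost

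*Protocol article*

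**What the plan says.** Quality of life is a secondary endpoint of the protocol article. Secondary objectives lists it for comparison according to treatment allocation, using the EQ-5D-5L "questionnaire at baseline and one-year follow-up". Secondary endpoints gives the same schedule, a "questionnaire administered at study enrolment and 12 months after surgical treatment of infection". The baseline is a recalled state: at enrolment, "patients will be asked to describe their health state immediately before index surgery". Consent may come up to seven days after surgery (Eligibility criteria), so the recall can span about a week.

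The analysis is given in one sentence: "The mean difference between quality of life scores at baseline and 12 months will be compared". Read with the objective, this means that the difference between the two scores is compared between arms. No model or covariate is named. Randomisation is stratified by treatment centre only (Assignment of interventions and allocation concealment).

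The end of the Bivariate analysis section refers to Additional file 1 for further secondary analyses. That file is not shown.

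**The concern.** A change score subtracts the whole of the baseline value, which amounts to fixing the regression slope of the 12-month score on baseline at 1. When the two scores are only moderately correlated, that over-corrects: noise in the baseline enters the estimate, and so does any chance imbalance between arms. ANCOVA estimates the slope from the data instead. Here the baseline is recalled, and surgery and a year of recovery lie between the two measurements, so a moderate correlation is plausible, though the article gives no value.

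At stake is the width of the confidence interval for one secondary endpoint. The information needed to narrow it is already being collected.

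**Working it through.** **The plan's own figure.** There is none for quality of life: no target difference, standard deviation, correlation or power. The only sample-size calculation (492, rounded up to 500) is for treatment failure and is not affected by this point.

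**Inputs.** From the article: 250 participants per arm (Sample size) and two EQ-5D-5L assessments. Assumed: equal standard deviation σ at both times, and baseline to 12-month correlation r of 0.3 to 0.6, with 0.2 and 0.8 as outer values.

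**Variance per participant.**

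- Change score: σ² + σ² − 2rσ² = 2σ²(1 − r).
- 12-month score adjusted for baseline: σ²(1 − r²).
- Ratio, change to adjusted: 2(1 − r) / [(1 − r)(1 + r)] = 2 / (1 + r).

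The ratio of confidence interval widths is the square root of the variance ratio. The number of participants with whom ANCOVA matches a 500-participant change-score analysis is 500 × (1 + r)/2.

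| r (assumed) | Change, in σ² | Adjusted, in σ² | Variance ratio | CI width ratio | ANCOVA total for equal precision |
|---|---|---|---|---|---|
| 0.2 | 1.60 | 0.96 | 1.67 | 1.29 | 300 |
| 0.3 | 1.40 | 0.91 | 1.54 | 1.24 | 325 |
| 0.5 | 1.00 | 0.75 | 1.33 | 1.15 | 375 |
| 0.6 | 0.80 | 0.64 | 1.25 | 1.12 | 400 |
| 0.8 | 0.40 | 0.36 | 1.11 | 1.05 | 450 |

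**Unequal standard deviations.** Let k be the 12-month standard deviation divided by the baseline one. In units of the baseline variance, the change score has variance k² + 1 − 2rk and the adjusted score k²(1 − r²). The first minus the second is 1 − 2rk + r²k² = (1 − rk)², which is never negative. Apart from the small cost of estimating the slope, ANCOVA is therefore never the less precise of the two, and they tie only when rk = 1. The variance ratios are:

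| k | r = 0.3 | r = 0.5 | r = 0.7 |
|---|---|---|---|
| 0.8 | 1.99 | 1.75 | 1.59 |
| 1.25 | 1.28 | 1.12 | 1.02 |

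The direction does not depend on the assumptions, but the size does: from 2% to 99% excess variance in this second table. None of these figures counts any further gain from adjusting for site.

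**The case against.** **The sentence may not exclude adjustment.** It names a quantity to compare, not a model. A change score analysed with baseline as a covariate gives exactly the same treatment effect as ANCOVA on the 12-month score, and Additional file 1 may specify this. That is fair, and it is why the point is modest. Still, the article does state a comparison, its plain reading is a difference in mean change, and a reader could follow it literally. Naming the adjusted analysis removes the doubt.

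**The change-score analysis is valid.** This stands in full. Over repeated randomisations it is unbiased, and its confidence interval already allows for chance baseline imbalance. The loss is in precision only.

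**Underpowered?** A reader might infer that the objective is underpowered. The article does not support that, because it sets no quality-of-life target. As an illustration, for an assumed difference of 0.25 standard deviations with 250 per arm and r = 0.5, power is about 0.80 with the change score and 0.90 with ANCOVA.

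**Measured too late?** Since "The intervention assessed in this study is the reduction of the duration of systemic antibiotic therapy", a reader might also infer that a 12-month score misses the weeks in which the arms differ, and that a null result would say nothing. The documents do not support this either.

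- The stated objective is quality of life at baseline and one year, and a 12-month score answers it. That score can also reflect the lasting consequences of treatment failure.
- Early antibiotic burden has its own instrument: "The advantage score is defined as the sum of predefined side effect scores at the first two follow-up timepoints". It is not a quality-of-life measure, but the early period is not ignored.
- Adding EQ-5D-5L at the 6-week point is a design preference. Participant timeline excludes trial-specific visits, so patient contact then is not assured, and a GP cannot supply a patient-reported score. The window is 5 to 7 weeks after randomisation, which itself falls up to a week after surgery. The questionnaire would therefore come about 5 to 8 weeks after surgery, when a course of the minimum four weeks would be over.

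**Conclusion.** The point holds as a matter of precision. The article states the EQ-5D-5L comparison as change from baseline and names no baseline adjustment. With equal standard deviations and an assumed correlation of 0.3 to 0.6, that costs 25% to 54% in variance, or a confidence interval about 12% to 24% wider, compared with adjusting the 12-month score for baseline. The correlation and standard deviations are assumptions. The direction of the loss follows from the algebra, apart from the negligible cost of estimating the slope. This is a low-stakes, free improvement to one secondary analysis: it corrects no bias, and the assessment schedule needs no change on this account.

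**What to change.** Replace the analysis sentence under Secondary endpoints with:

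*The 12-month EQ-5D-5L score will be compared between arms by ANCOVA adjusted for baseline EQ-5D-5L and study site, with a 95% confidence interval.*

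Site is included because it is the randomisation stratum. If Additional file 1 already specifies baseline adjustment, it is enough to bring the article's wording into line with it. The cost is wording only: no new data, contacts or participants. Mean change by arm can still be reported descriptively.

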### Blinded Endpoint Committee

A blinded Endpoint Committee will comprise three independent clinicians with specialist training in orthopaedic surgery or clinical infection. The blinded Endpoint Committee will remain unaware of participants’ treatment allocation. Any symptoms or signs identified from the hospital notes or when the participant is reviewed at follow-up that, in the opinion of the study clinicians, may meet the definition of treatment failure, will be reported to the Committee. Additionally, the following clinical events during the trial follow-up period will be reported, so that the Endpoint Committee can assess whether an endpoint has occurred:
Readmission to hospital for investigation or treatment of illness that may be associated with the site of incident infection;Unplanned reoperation at the anatomical site of infection;Wound dehiscence, discharge or appearance of new sinus at the site of incident infection;Prescription of additional systemic antibiotics for orthopaedic infection at the incident anatomic site after completion of systemic antibiotic treatment for index orthopaedic infection;Mortality during the trial follow-up period;Concern from the local study clinicians that there has been a recurrence of infection, where none of the above criteria have been met.

